## Abstract

**Background:**

Early detection of cancer and precise recurrence monitoring remain major unmet needs in oncology. Conventional screening is limited to a few cancer types, leaving nearly half of cancers without established programs. Multi-cancer early detection (MCED) tests based on circulating tumor biomarkers have shown promise, but sensitivity for early-stage remains a challenge. In parallel, detection of molecular residual disease (MRD) using circulating tumor DNA (ctDNA) has emerged as a powerful prognostic and predictive tool, though current assays remain limited in sensitivity and specificity. This study aims to integrate multi-omics data to develop more refined and highly sensitive MCED and MRD assays.

**Methods:**

This study leverages clinical information and biospecimens from patients with cancer and cancer-naïve individuals. Samples from patients with cancers will be derived from the MONSTAR-SCREEN-3 study, while those from cancer-naïve individuals will be obtained from the Tohoku Medical Megabank Project. Comprehensive analyses will include whole-genome sequencing (WGS), whole-exome sequencing (WES), whole-transcriptome sequencing (WTS), proteomics, metabolomics, and microbiome profiling using stool and saliva. Artificial intelligence (AI)-based multi-omics integration will be performed to develop novel MCED and MRD assays and to evaluate their clinical performance. The primary endpoints are the sensitivity and specificity of MCED and MRD assays.

**Discussion:**

This is the first large-scale study to integrate comprehensive multi-omics profiling with AI for MCED and MRD assay development. The findings are expected to advance precision oncology by improving early diagnosis and recurrence monitoring.

**Trial registration:**

UMIN000053815, approved by the Institutional Review Board of the National Cancer Center Hospital East.

## Introduction

Cancer is responsible for approximately 10 million deaths annually worldwide and remains the leading cause of death in Japan, with about one million new cases and 380,000 deaths each year. Patients diagnosed at an early stage have a favorable chance of long-term survival, while those diagnosed at an advanced stage experience markedly reduced survival rates [1, 2]. These findings underscore the critical importance of early diagnosis and prompt therapeutic intervention in improving patient outcomes. Even in developed countries such as the European Union (EU), the United States, and Japan, population-based cancer screening programs are currently established for only a limited number of cancer types, including breast, colorectal, gastric, lung, and cervical cancers. However, these screening methods are often neither simple nor easily accessible, and challenges such as procedural invasiveness and low participation rates are common across regions. Moreover, cancers other than these limited types still account for the majority of cancer-related deaths, representing approximately 63.2% in the United States, 79.4% in the EU, and 51.3% in Japan (Fig. 1) [3–5]. As a result, many cancers are diagnosed at advanced stages, leading to poor outcomes. Therefore, there is an urgent need to develop new, simple, and minimally invasive detection approaches capable of identifying a broader range of cancers at earlier, more treatable stages.

**Fig. 1 Fig1:**
[figure not shown]
Proportion of cancer deaths attributable to currently screenable cancers versus other cancers in the United States, European Union, and Japan. Population-based cancer screening programs in these regions primarily target a limited number of cancers. As shown, these screened cancers account for less than half of all cancer deaths, while cancers without established screening methods represent the majority of deaths. Abbreviations: *US* the United States, *EU* European Union

In this context, blood-based analyses using plasma samples have emerged as a promising approach for both early cancer detection and post-treatment disease monitoring. Recently, multi-cancer early detection (MCED) tests that analyze tumor-derived biomarkers in blood, such as genomic alterations, abnormal DNA methylation, and cell-free DNA fragmentation patterns, have been developed as a less invasive and more accessible screening approach. Large-scale prospective studies have demonstrated the clinical potential of MCED testing, revealing its ability to facilitate early diagnosis even in cancer types for which conventional screening methods are unavailable. Although existing studies have targeted different cancer types and employed diverse omics approaches, making direct comparison across studies challenging, the accumulated evidence collectively suggests the clinical utility of MCED as a promising approach for population-level cancer screening. Despite these encouraging findings, challenges remain, particularly the need to improve sensitivity for early-stage cancers. In parallel, the detection of molecular residual disease (MRD) in post-treatment patients has emerged as a promising approach for identifying early recurrence after curative therapy. In particular, MRD analysis using circulating tumor DNA (ctDNA) has been shown to be useful for predicting recurrence risk and treatment response across various cancer types. However, in low-shedding tumors, the sensitivity and specificity of existing assays remain limited, making it challenging to reliably detect minimal residual disease or early relapse.

Thus, while both MCED and MRD hold considerable clinical promise, current technologies still face challenges in achieving sufficient sensitivity and specificity. Most previously reported assays have been based on one or two omics layers, which may not adequately meet these clinical demands. In the present study, by integrating multiple layers of omics data, including whole-genome sequencing (WGS), whole-exome sequencing (WES), whole-transcriptome sequencing (WTS), proteomics, metabolomics, and microbiome, with AI-driven analytical approaches, we aim to develop MCED and MRD assays with greater precision and sensitivity. To ensure the robustness and reproducibility of these analyses, the majority of platforms, workflows, and analytical pipelines have been standardized as much as possible, thereby minimizing batch effects and maintaining data integrity.

This study (UMIN000053815) is conducted on the basis of two large-scale cohort platforms in Japan: MONSTAR-SCREEN-3 study, a nationwide molecular screening project for cancer patients, and the Tohoku Medical Megabank Organization (ToMMo), which maintains comprehensive multi-omics data from the general population. By integrating multi-omics data, the study aims to develop highly sensitive MCED and MRD assays.

## Methods/design

### Study design

This study was conducted utilizing two platforms in Japan: MONSTAR-SCREEN-3 and the ToMMo. These cohorts provide extensive clinical and multi-omics resources that enable analyses for the development of high-performance MCED and MRD assays.

MONSTAR-SCREEN-3 (UMIN000053975), launched in 2024, is a nationwide multi-center project comprising three cohorts (advanced solid tumors, curatively resectable solid tumors, and hematologic malignancies) enrolling approximately 3,200 patients. Through multi-layered omics analyses, including whole-genome sequencing (WGS), whole-transcriptome sequencing (WTS), proteomics, metabolomics, spatial transcriptomics, and microbiome profiling, molecular and clinical imaging data are integrated to develop next-generation AI-based biomarkers.

ToMMo, established in 2012, is one of Japan’s largest biobank and population cohort research initiatives, originally found to support medical reconstruction following the Great East Japan Earthquake and to advance precision medicine. The project has enrolled approximately 150,000 population-based participants, systematically collecting a wide range of biospecimens (blood, urine, saliva, breast milk, and peripheral blood mononuclear cells) and integrating these materials into comprehensive genomic and omics databases for future medical innovation.

Using existing retrospective clinical and multi-omics data, we will develop AI classifiers for cancer detection and tissue-of-origin prediction based on data from cancer patients in the MONSTAR-SCREEN-3 study and cancer-naïve individuals in the ToMMo cohort. These classifiers will guide the development of MCED and MRD assays, whose clinical performance will then be validated using archived specimens from the MONSTAR-SCREEN-3 study and prospectively collected samples from the ToMMo cohort (Fig. 2).

**Fig. 2 Fig2:**
[figure not shown]
Overview of the study. Using multi-omics data from 1000 cancer patients in the MONSTAR-SCREEN-3 study and 1000 cancer-naïve individuals in the ToMMo cohort, cancer signal origin and cancer signal classifiers will be developed to guide the creation of MCED and MRD assays. Clinical performance studies will then be conducted using samples from 200 cancer patients and 200 cancer-naïve individuals. Abbreviations: *WES* whole-exome sequencing, *WTS* whole-transcriptome sequencing, *WGS*, whole-genome sequencing, *SOP* standard operating procedure, *AI* artificial intelligence, *MCED* multi-cancer early detection, *MRD* minimal residual disease, *CRC* colorectal cancer, *GC* gastric cancer, *PC*, pancreatic cancer, *EC* esophageal cancer, *BTC* biliary tract cancer, *HCC* hepatocellular carcinoma, *HNC* head and neck cancer, *UC* urothelial carcinoma, *RCC* renal cell carcinoma, *BC* breast cancer, *OC* ovarian cancer, *EnC* endometrial cancer, *CC* cervical cancer, *L* leukemia, *MDS* myelodysplastic syndromes

## Study population

### Development of AI classifiers for cancer detection and cancer-of-origin prediction

This study will first develop artificial intelligence (AI) classifiers to predict the presence of cancer and identify the tissue of origin using multi-omics data obtained from the MONSTAR-SCREEN-3 study and the ToMMo cohort. In total, multi-omics data from approximately 1,000 consecutive cancer patients (MONSTAR-SCREEN-3) and 1,000 background-aligned cancer-naïve individuals (ToMMo) across about 15 cancer types will be analyzed. Up to 1,000 multi-omics datasets from the MONSTAR-SCREEN-3 study, including tumor WGS/WES, WTS, germline WGS, plasma proteome/metabolome, and oral/gut microbiome data, will be analyzed alongside approximately 1,000 background-matched cancer-naïve individuals from the ToMMo cohort undergoing comparable profiling. Clinical information such as age and sex will be retrieved from the ToMMo database. Plasma proteomic analysis will be performed on approximately 1,000 archived plasma samples from the ToMMo biobank using the O-link HT system. All analyses will be conducted with approval from the ToMMo Sample and Data Access Committee. The datasets obtained from both the MONSTAR-SCREEN-3 study and the ToMMo cohort will be integrated to develop deep learning-based AI classifiers, including the Cancer Signal Classifier (detecting the presence of cancer) and the Cancer Signal Origin Classifier (predicting the tissue of origin). Supervised machine learning and deep learning models will be developed and integrated using ensemble techniques. The integrated dataset will be divided into training and internal validation sets to optimize model performance and minimize overfitting. Multi-omics data integration will be employed to identify features associated with cancer presence and tissue of origin. These features will be systematically evaluated to assess their compatibility with ctDNA-based assays. Based on this evaluation, ctDNA-compatible signatures will be selected and used for the development of blood-based MCED and MRD assays. The resulting models are intended to support scalable cancer detection and longitudinal disease monitoring.

### Clinical performance test of MCED and MRD assays

The clinical performance of MCED and MRD assays will be evaluated using approximately 200 samples, each from the MONSTAR-SCREEN-3 study and the ToMMo cohort. In the MONSTAR-SCREEN-3 study, approximately 200 archived plasma samples collected from participants in the main study will be analyzed for ctDNA. In the ToMMo cohort, up to 200 participants will be newly recruited after obtaining written informed consent. In addition to routine ToMMo blood collection (36 mL), an additional 10 mL of blood will be drawn using a ccfDNA PAXgene tube for ctDNA analysis.

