### Specimen collection and processing

To minimize batch effects across study cohorts, specimen collection and processing procedures were standardized as much as possible between the MONSTAR-SCREEN-3 study and the ToMMo cohort. For proteomic and metabolomic analyses, blood samples were collected in EDTA-2Na tubes, kept at 4 °C, and centrifuged within 8 h of collection at 2,330 × g for 10 min at 4 °C. The obtained plasma was aliquoted and stored at – 80 °C. For salivary microbiome analysis, saliva samples were collected using Mini centrifuge tubes and stored at – 80 °C immediately after collection. Tumor specimens in the MONSTAR-SCREEN-3 study were collected and stored in accordance with a standardized protocol, ensuring consistency in tissue handling and preservation. WES and WTS analyses of these tumor samples were centrally performed by GxD company, using harmonized pipelines to maintain analytical uniformity. For ctDNA analysis, blood samples were collected using PAXgene Blood ccfDNA tubes. Samples were centrifuged within 7 days after collection: the first centrifugation was performed at 1,900 × g for 15 min at 15–25 °C, followed by a second centrifugation at 1,900 × g for 10 min at 15–25 °C. The separated plasma was stored at − 80 °C until analysis. Although the analytical methods for WGS and fecal microbiome analyses differed between the MONSTAR-SCREEN-3 study and the ToMMo cohort, systematic biases were minimized during AI classifier development by applying standardized feature scaling across datasets.

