A notable strength of this study is the rigorous standardization of sample collection and analytical workflows across cohorts to minimize technical batch effects, which have historically confounded large-scale multi-omics studies [13, 14]. In our protocol, tissue-derived samples for WTS and WES are collected strictly in accordance with predefined SOPs and analyzed by a single company using a unified sequencing platform. Similarly, proteomic, metabolomic, and microbiome analyses are performed with harmonized logistics and analytical pipelines wherever feasible. This approach not only reduces non-biological variation, but also establishes a robust and harmonized multi-omics dataset that may serve as a reference standard for comparative analyses between cancer and cancer-naïve populations. Such a framework is expected to enhance the robustness, reproducibility, and clinical interpretability of AI-based classifiers.

Furthermore, the integration of multi-omics data through AI-driven modeling embodies a *trans-omics* approach, enabling the capture of complex cross-layer interactions that conventional single- or dual-omics assays fail to resolve. Such interactions may underlie early tumorigenic processes or subtle host–tumor dynamics, thereby enhancing sensitivity for early cancer detection and MRD monitoring.

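### In the primary performance test every cancer sample is archived and every control sample newly collected, so cohort, collection programme and possibly storage duration are aligned with disease status

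*Protocol article*

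**What the plan says.** Under Clinical performance test of MCED and MRD assays, the article takes its cancer samples from storage: "approximately 200 archived plasma samples collected from participants in the main study will be analyzed for ctDNA". For the cancer-naïve side, "up to 200 participants will be newly recruited after obtaining written informed consent", and from them "an additional 10 mL of blood will be drawn using a ccfDNA PAXgene tube for ctDNA analysis". Study design repeats the contrast, naming "archived specimens from the MONSTAR-SCREEN-3 study and prospectively collected samples from the ToMMo cohort" as the validation material. The Fig. 2 legend gives the size: "Clinical performance studies will then be conducted using samples from 200 cancer patients and 200 cancer-naïve individuals". Under Endpoints, clinical performance, including sensitivity and specificity, is the primary endpoint.

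Specimen collection and processing describes one ctDNA procedure with no stated difference between cohorts: PAXgene ccfDNA tubes, two spins at 1,900 × g, and plasma kept at −80 °C until it is analysed. On timing it says "Samples were centrifuged within 7 days after collection". The Discussion claims as a strength "rigorous standardization of sample collection and analytical workflows across cohorts".

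**The concern.** No sample in this test set is an archived control or a newly collected case. Anything that differs between the two programmes, or that changes in plasma with time in the freezer or time before the first spin, is therefore inseparable from disease status. If such a factor raises the assay score in stored case plasma, it is counted as sensitivity; if it lowers the score, true sensitivity is understated. The controls cannot reveal either effect, because none of them shares the cases' source.

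At stake is the main result of the study. The planned 95% confidence intervals (Statistical analysis) describe sampling variation only, so a shift of this kind would not show in them.

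**Working it through.** **Step 1. What coincides with disease status.**

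| Feature | Cases (about 200) | Controls (up to 200) | Aligned with disease? |
|---|---|---|---|
| Cohort and programme | MONSTAR-SCREEN-3 | ToMMo | Yes, fully |
| Archived or new | Archived | New draw | Yes, fully |
| Tube, spins, freezing | PAXgene, two spins, −80 °C | Same, as far as stated | No |
| Storage duration | Not stated | Not stated | Possibly |
| Draw-to-spin time | Up to 7 days | Up to 7 days | Unknown |
| Assay run | Not stated | Not stated | Unknown |

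**Step 2. Do the stated safeguards reach this test?** The common ctDNA procedure fixes method but not storage duration, and a 7-day limit lets two programmes comply with quite different draw-to-spin times. The feature scaling in Specimen collection and processing concerns WGS and fecal microbiome data during classifier development, not ctDNA in the performance test. The single-company analysis concerns WES and WTS of tumour tissue.

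**Step 3. Bound on storage.** Study period gives enrolment from 27 February 2024 and study end on 31 March 2027, about 37 months apart. This bounds case storage only if a sample was drawn on the first day and assayed on the last. Control draw dates are not given, so the difference between groups may lie anywhere from none to that bound.

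**Step 4. Sampling precision.** The article gives no precision figure for the 200/200 test, so there is none to reproduce. Taking the early-stage sensitivities of 30–50% cited in the Discussion as benchmarks, Clopper-Pearson 95% intervals at n = 200 are:
- 60/200 (30%): 23.7–36.9%
- 100/200 (50%): 42.9–57.1%

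**Step 5. Illustration of a shift in cases only.** Assume normally distributed scores, a fixed threshold, and a handling-related shift of d SD in cases. The values of d are assumptions. Observed sensitivity = Φ(Φ⁻¹(true sensitivity) + d).

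| True sensitivity | d = −0.3 | d = −0.1 | d = +0.1 | d = +0.3 |
|---|---|---|---|---|
| 30% | 20.5% | 26.6% | 33.6% | 41.1% |
| 50% | 38.2% | 46.0% | 54.0% | 61.8% |

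At ±0.1 SD the result stays inside the interval of step 4; at ±0.3 SD it falls outside. At 50% the break-even is about 0.18 SD, since Φ(0.18) = 0.571, the upper limit.

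**Step 6. A milder, one-directional illustration.** Suppose handling alone turned a share a of otherwise negative stored samples positive, with a = 1–5% (assumed, with no source in the document). Observed sensitivity at a true 50% is 0.50 + 0.50a, which is 50.5% to 52.5%. That bias lies well inside the sampling interval.

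**The case against.** The strongest reply is that the article condenses a fuller protocol, that both sets of plasma follow one procedure, and that the sizes above are assumed. Much of this stands, and it rules out several stronger readings that a reader might infer:

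- **That assay run coincides with disease status.** No section allocates runs. Both sets are frozen until analysis, so joint runs are possible, and run layout and blinding are details an article may leave to the full protocol.
- **That archived plasma is compared with fresh plasma.** The controls are newly collected but also stored at −80 °C. Only the duration of storage may differ, and the single enrolment window permits overlap.
- **That transport time is known to differ.** One 7-day limit is stated, and no draw-to-spin distribution is given for either cohort.
- **That the reported specificity is biased.** With the 1–5% artefact, specificity of 99% would become 0.99(1 − a), or 98.0–94.1%, in controls stored like the cases: 4.0 to 11.9 false positives in 200 instead of 2. Such controls are hypothetical. The reported 99% could still be right for newly drawn blood, which is closer to screening use.
- **That all 200 archived samples are reference-positive for both assays.** The article does not say so for MRD.

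What the reply does not remove is the stated source of the two groups. That is a design choice made in two sections, and further laboratory detail in a fuller document would not change it.

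**Conclusion.** The point holds in a limited form. Cohort, collection programme and archived-versus-new status are fully aligned with disease status in the test that yields the primary endpoint; storage duration possibly is as well. Sensitivity and the case-control contrast can therefore be biased, and this test set cannot separate that bias from disease.

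Neither the size nor the direction can be determined from the document. Under the assumed shifts, the effect on sensitivity runs from 0.5 points (1% artefact) to about 12 points in either direction (0.3 SD at a true 50%), against a sampling half-width of about 7 points. These figures show what could pass unseen, not what is expected. The change is worth making because it is cheap, concerns the primary endpoint, and cannot be made in full once the samples have been assayed.

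**What to change.** Amend Clinical performance test of MCED and MRD assays to state that:

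1. For the MCED part, archived case samples are selected so that their storage times overlap those of the controls, with selection made within cancer type and stage to preserve case mix.
2. Cases and controls are assayed together in mixed, randomly ordered batches, with the laboratory blind to group.
3. Sensitivity is reported by storage time and by draw-to-spin time, and control scores by draw-to-spin time.
4. Confounding by cohort remains after these steps and limits interpretation. The standardization claim in the Discussion should carry the same qualification.

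The cost is laboratory scheduling, because samples wait until batches can be mixed, some restriction on which archived cases can be used, and one extra table. No additional blood draws are needed.

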### Specimen collection and processing

To minimize batch effects across study cohorts, specimen collection and processing procedures were standardized as much as possible between the MONSTAR-SCREEN-3 study and the ToMMo cohort. For proteomic and metabolomic analyses, blood samples were collected in EDTA-2Na tubes, kept at 4 °C, and centrifuged within 8 h of collection at 2,330 × g for 10 min at 4 °C. The obtained plasma was aliquoted and stored at – 80 °C. For salivary microbiome analysis, saliva samples were collected using Mini centrifuge tubes and stored at – 80 °C immediately after collection. Tumor specimens in the MONSTAR-SCREEN-3 study were collected and stored in accordance with a standardized protocol, ensuring consistency in tissue handling and preservation. WES and WTS analyses of these tumor samples were centrally performed by GxD company, using harmonized pipelines to maintain analytical uniformity. For ctDNA analysis, blood samples were collected using PAXgene Blood ccfDNA tubes. Samples were centrifuged within 7 days after collection: the first centrifugation was performed at 1,900 × g for 15 min at 15–25 °C, followed by a second centrifugation at 1,900 × g for 10 min at 15–25 °C. The separated plasma was stored at − 80 °C until analysis. Although the analytical methods for WGS and fecal microbiome analyses differed between the MONSTAR-SCREEN-3 study and the ToMMo cohort, systematic biases were minimized during AI classifier development by applying standardized feature scaling across datasets.

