### Eligibility criteria

Participants who, as of March 2026, are enrolled in the MONSTAR-SCREEN-3 study have not withdrawn consent, and have not declined the secondary use of their clinical data or biospecimens (1). Participants in the MONSTAR-SCREEN-3 study must be 18 years of age or older (2). Individuals who participated between May 2013 and September 2025 in either the ToMMo Three-Generation Cohort Study or the Community-Based Cohort Study, who have not withdrawn consent, and have not refused the secondary use of their data or samples will also be eligible. For participants undergoing additional blood collection for clinical performance testing, written informed consent for this study will be voluntarily obtained (3). ToMMo participants must have no history of malignant tumors (4) and must be between 20 and 75 years of age at the time of consent (5). To ensure background comparability, the age and sex distributions of ToMMo participants will be strictly adjusted to match those of patients with solid tumors enrolled in the previous MONSTAR-SCREEN-2 study (UMIN000043899).

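### Cancer status and cohort coincide for every sample, so feature scaling cannot have minimized the bias from WGS and fecal microbiome methods that differed between cohorts

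*Protocol article*

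**What the plan says.** The Methods part of the abstract fixes the two sources. For the cases it says: "Samples from patients with cancers will be derived from the MONSTAR-SCREEN-3 study". For the controls it says that "those from cancer-naïve individuals will be obtained from the Tohoku Medical Megabank Project". Eligibility criteria adds that "ToMMo participants must have no history of malignant tumors". The section on development of AI classifiers merges about 1,000 patients and 1,000 controls from these sources and splits the merged data into training and internal validation sets. The section on the clinical performance test uses the same two sources again: about 200 archived MONSTAR-SCREEN-3 plasma samples and up to 200 newly recruited ToMMo participants.

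Specimen collection and processing describes common handling for plasma proteome and metabolome, saliva and ctDNA, and then makes an exception: "Although the analytical methods for WGS and fecal microbiome analyses differed between the MONSTAR-SCREEN-3 study and the ToMMo cohort", followed by the assurance that "systematic biases were minimized during AI classifier development by applying standardized feature scaling across datasets". No other remedy is named for these two layers.

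The classifier section lists the case data as "including tumor WGS/WES, WTS, germline WGS, plasma proteome/metabolome, and oral/gut microbiome data" and describes the controls as "individuals from the ToMMo cohort undergoing comparable profiling". ToMMo eligibility covers "Individuals who participated between May 2013 and September 2025"; Study design says that MONSTAR-SCREEN-3 was launched in 2024.

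**The concern.** If every case is from one cohort and every control from the other, any measurement difference between the cohorts is fully confounded with the label. A classifier rewarded for separating cases from controls is rewarded equally for separating the cohorts. For two layers the article itself says that the methods differed, so a measurement difference there is to be expected, and the only stated protection is scaling.

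At stake is which features are taken to mark the presence of cancer. These go through a ctDNA-compatibility evaluation, and the signatures that pass are used to build the MCED and MRD assays. That evaluation asks whether a feature can be measured in ctDNA, not whether its association with cancer is real.

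**Working it through.** The plan gives no figure for this bias, so there is none to reproduce. The check is structural, followed by an illustration of size.

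**1. Does cohort equal label?** Cases: MONSTAR-SCREEN-3 only. Controls: ToMMo only, with no history of malignancy. This holds in development and in the performance test. No described sample breaks the identity, so the data alone cannot separate a cohort effect from a cancer effect.

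**2. What can scaling do?** For one feature, let the case mean minus the control mean be b + s, where b is the true cancer effect and s the platform shift, with common standard deviation σ.

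- Pooled scaling uses one mean m and one standard deviation for everyone. The scaled difference is [(μ₁ − m) − (μ₀ − m)]/SD = (b + s)/SD. Cases and controls undergo the same transformation, so their separation in SD units, and hence the AUC, is unchanged.
- Within-cohort scaling sets the mean to zero in each cohort. The scaled difference is 0: s is gone, and so is b. Because cohort equals label, this is scaling within label.

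Neither version removes s while keeping b.

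**3. How large could it be?** Assume no biology (b = 0), K independent normal features with equal variance, and a shift of d SD in each. The best linear score has AUC = Φ(√K · d/√2). For K = 50, √50/√2 = 5, so AUC = Φ(5d).

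| K | d (SD) | Argument | AUC |
|---|---|---|---|
| 50 | 0.05 | 0.25 | 0.60 |
| 50 | 0.1 | 0.50 | 0.69 |
| 50 | 0.2 | 1.00 | 0.84 |
| 10 | 0.2 | 0.447 | 0.67 |

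K and d are assumptions; the documents give neither.

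**4. Simulation.** Assumptions: 1,000 cases and 1,000 controls, 100 normal features, shifts drawn from N(0, s²), a 70/30 split of the merged data, a ridge-penalized linear classifier, 20 repeats, and scaling parameters taken from the training part.

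| s (SD) | Internal AUC, no cancer signal | Internal AUC, signal of 0.2 SD in 20 features | Same model, cases and controls from one cohort, same signal |
|---|---|---|---|
| 0 | 0.50 | 0.70 | 0.70 |
| 0.05 | 0.58 | 0.73 | 0.68 |
| 0.1 | 0.72 | 0.80 | 0.64 |
| 0.2 | 0.90 | 0.93 | 0.60 |
| 0.3 | 0.98 | 0.98 | 0.57 |

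These columns use pooled scaling. With no cancer signal, the same models have an AUC of about 0.50 when cases and controls share a cohort. Within-cohort scaling gives about 0.50 in every scenario (0.49 to 0.51), including those with real signal. As the shift grows, internal AUC rises while same-cohort performance falls.

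**5. Would a planned check reveal it?** The internal validation set is a random part of the same merged data and carries the same shift. The performance test again compares MONSTAR-SCREEN-3 with ToMMo, and adds a contrast of archived with newly drawn blood. Neither contains cases and controls from one source.

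**The case against.** The strongest reply is that the exposure is limited. Plasma, saliva and ctDNA handling was harmonized, and ToMMo age and sex are adjusted to an earlier MONSTAR cohort. Only ctDNA-compatible signatures go forward, so fecal microbiome artifacts are unlikely to reach the final assays. The primary endpoint is measured with a ctDNA assay using one tube type and one centrifugation protocol, so a WGS platform artifact need not recur there and could even lower performance. The article says minimized, not eliminated. All of this stands as a limit on reach and size. None of it makes scaling a remedy for the two layers that differed, or breaks the identity of cohort and label.

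A reader might infer more than the documents support:

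- **That case-only tumor layers give away the label.** Cancer-naïve people have no tumor, so comparable profiling cannot include tumor sequencing. But the article does not say that these layers enter the Cancer Signal Classifier. The point applies only if they do; the wording may refer to shared layers only.
- **That storage time separates the groups.** The 2013 to 2025 window is a period of participation, not of blood draw. Storage time may track the label, but this is not shown.
- **That artifacts pass straight into the assays.** The ctDNA-compatibility step lies between.
- **That the planning AUC of 0.85 is explained by artifact.** The value 0.84 is one point in a wide range that depends on assumed inputs. The illustration also uses mean shifts and linear classifiers; it does not show how the planned deep-learning ensembles would behave.

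**Conclusion.** The claim that scaling minimized the bias is wrong as written. For WGS and fecal microbiome, cohort and cancer effects cannot be separated in these data, and neither the internal split nor the 200 + 200 test can show how much of the apparent performance is cohort. This follows from the design and needs no numerical assumption.

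The size is unknown. Under the stated assumptions, artifact alone gives an AUC of 0.60 to 0.84 for 50 features and shifts of 0.05 to 0.2 SD. Modest shifts could therefore matter, but the documents do not show that they are present. The supported conclusion is that the classifier can learn cohort, not that it will, and that sensitivity, specificity and AUC may be inflated.

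**What to change.** 1. Delete the statement that scaling minimized the bias. Say instead that cohort and cancer effects cannot be separated for layers assayed differently.
2. Base the primary Cancer Signal Classifier, and the selection of cancer-presence features, on layers confirmed to be collected and assayed alike in both cohorts. Candidates are plasma proteome, plasma metabolome and salivary microbiome. Confirmation is needed: the article names a proteomic platform only for ToMMo plasma and none for the metabolome. Use tumor WES/WTS, WGS and fecal microbiome for tissue of origin within MONSTAR-SCREEN-3. Report any all-layer cancer-presence model as exploratory.
3. Screen the retained plasma features for association with storage time within ToMMo. This is a partial check, since storage time may also track participant characteristics.
4. State that cohort still equals label in the retained layers and in the 200 + 200 test, so that sensitivity, specificity and AUC may be inflated.

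The cost is revised wording, one screening analysis and a narrower primary model, with no new recruitment. The price is fewer layers, probably a lower AUC, and fewer ctDNA-compatible candidates for the cancer-presence part of MCED, because none of the three candidate layers is itself a ctDNA layer. The change reduces the confounding but does not cure it. Only cases and controls from the same source, run in mixed batches, would do that, and this is a larger change.
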